### Recruitment

During the initial PN consultation with the index patient, the healthcare professional will assess eligibility for the study for all patients with a laboratory positive test result for chlamydia or a clinical diagnosis of NGU/epididymo-orchitis (men) or PID/cervicitis (women). During the intervention phase, the healthcare professional will offer eligible patients APT in addition to standard methods of PN. The trial data manager will monitor recruitment and patient uptake of the APT intervention throughout the trial period supplying monthly recruitment figures to the Trial Management Group (TMG) and Data Monitoring Committee (DMC).

### Randomisation/allocation sequence

The random allocation of clinics, to intervention or control arm first, was conducted through random permutation within strata, using computer-generated random numbers in Stata V.15 software. In four strata, the two clinics were part of one NHS trust and were considered as pairs. One stratum contained five clinics from large cities and another contained three clinics from smaller settlements. Given the odd numbers of clinics in these strata, we used random assignment to determine whether two or three clinics would implement the intervention first in the larger stratum (correspondingly two or one in the smaller stratum to ensure balance). One further clinic, the last (17th) to start recruitment was allocated through simple randomisation, giving a total of nine clinics allocated to implement the intervention first and eight to first follow routine practice. To remove the potential for allocation bias arising because allocation codes were generated after clinics had already been recruited to the trial, one statistician generated the allocation codes and another randomly permuted the clinic names within the strata. Only then, a third person matched the two to reveal the allocations and inform the clinic manager.

### Blinding

Blinding of allocation will not be possible for healthcare professionals, patients or research staff. A statistician blinded to allocation will replicate the analysis of the primary outcome.

### Procedure for collecting data

Healthcare professionals will record their consultations in real time and download data needed for clinical purposes into the patient’s clinic record. They will use RELAY, a bespoke data collection tool. RELAY is a secure web-based data collection platform, which incorporates different interfaces allowing specified levels of access to healthcare professionals, RHAs, data manager, trial manager and the research team. It is hosted on secure servers and compliant with NHS data storage requirements. We developed RELAY for the LUSTRUM trial, based on previous versions of data collection tools in our pilot studies of APT.^25 26^

### Statistical analysis

Analysis will be by intention-to-treat. For the primary, and other quantitative outcomes, we will fit random effects models with fixed effects for clinic and intervention condition, together with a random effect to acknowledge the clustering of index patients for each combination of clinic and for each period.^34^ The primary and key secondary outcomes are binary, so we will use logistic regression models. The intervention effect will be expressed as an OR with 95% CI. Models for secondary outcomes with outcomes quantified for each sexual contact will include additional random effects for the index patient.

We anticipate loss to follow-up of around 40% of participants, raising potential concerns over bias. Before conducting our analysis of the primary outcome we will analyse predictors of follow-up from among a prespecified list of characteristics of the index patients that will be recorded at baseline and which are considered to be likely predictors of the primary outcome. In the primary analysis of the primary outcome we will include these as covariates in our regression model along with any other key predictors of the outcome. This approach should reduce bias from loss to follow-up but we will also conduct further sensitivity analyses based on multiple imputation in which we will allow those lost to follow-up to be more, and then less, likely to be chlamydia positive at 3 months than those not lost to follow-up with the same baseline covariates. These sensitivity analyses will follow the approach of Carpenter *et al*,^35^ to assess the robustness of our conclusions to different prespecified assumptions about missing data.

#### Exclusions from analyses

The intervention is implemented at the clinic level and applied to all eligible patients with service-level, rather than individual, consent. Patients can opt-out of their data being used for research (see online supplementary file 1). Once a clinic has begun the allocated intervention then all eligible patients added to the RELAY web tool will be included in analysis, following the spirit of an intention-to-treat analysis and the all-randomised population. However, in the unlikely event of a substantial period in which any clinic is subsequently unable to implement the intervention for any reason then we will also conduct an analysis that only includes patients attending the clinic while it is able to offer the intervention, in the spirit of a per-protocol analysis and a protocol compliant population. The inclusion of patients in analysis will not be influenced by whether the patient does or does not take up the offer of APT.

10.1136/bmjopen-2019-034806.supp1Supplementary data

Patients who present with conditions managed at first attendance as presumptive urogenital chlamydia but who subsequently are found to have negative chlamydia tests will be excluded from analyses.

### Trial timeline

There will be a 4-month run in period (July–October 2018), consisting of rolling clinic set-up including training for healthcare professionals and a period of at least 2 weeks of baseline data collection when healthcare professionals will use RELAY to record standard PN data. Research staff will monitor completeness of baseline data collection. The data will be used at the end of the trial to help interpret the trial findings. Then half of the clinics will enter intervention phase while the other half enter control phase, according to the randomisation schedule. The trial is planned to start 22 October 2018.

At the end of the first 6-month trial phase (October 2018–April 2019) there will be a 2-week washout period where clinics will not offer APT to patients and follow their standard PN practice procedures. Clinics which start with the control phase will also observe the 2-week washout to align the trial time periods. Then clinics cross over to the opposite arm (intervention or control) for phase two (for 6 months, May–November 2019); patient recruitment is planned to end 17 November 2019. The total duration of the trial will be 19 months, allowing for a 3-month follow-up period to enable outcome data collection to be completed for all patients in the second trial phase. Clinics which do not start phase one of the trial in November 2018 will complete recruitment in November 2019 and trial phases will be condensed. The LUSTRUM programme as a whole runs from April 2016 to March 2021.

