Box 1Overview of accelerated partner therapy (APT) for index patientsIndex patient has partner notification (PN) consultation with healthcare professional (HCP); HCP assesses eligibility for APT.Eligible index patient is offered APT alongside the clinic’s other standard PN options. The patient can choose different methods for different partners.Index patient telephones or messages sex partner (with or without the HCP present, according to preference) to offer immediate telephone assessment by the HCP.Index patient waits in clinic while the HCP conducts APT telephone consultation in private with sex partner.Index patient is informed that they will receive a follow-up telephone call in 2 weeks and they will either receive a chlamydia self-sampling postal kit in 12–16 weeks (preferred), or they may re-attend the clinic for testing.Two-week follow-up: research health adviser (RHA) telephones index patient to find out about PN outcomes with partner(s), to remind them of the repeat test, and to invite them to be contacted about taking part in a telephone interview regarding their experiences of APT (process evaluation).12 weeks: index patient is sent a personalised text reminder about repeat test.13 weeks: index patient is sent a self-sample kit by The Doctors Laboratory (TDL). Index patient returns self-collected sample or attends clinic for repeat testing. S/he receives results either via text message from TDL (negative results) or using routine clinic systems (positive or equivocal results). Positive results are managed according to routine clinic protocol. If the index patient does not return a self-sample or attend clinic for repeat testing, they receive a personalised text reminder 8 days after the self-sample kit is sent out, followed by a telephone call from the RHA 13 days after the self-sample kit is sent out. Self-samples received >24 weeks post-PN interview are excluded.

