### Outcomes

The primary clinical outcome is the proportion of index patients with a positive test result for *C. trachomatis* 12–16 weeks after the PN consultation. A repeated positive test result after treatment is a proxy for re-infection from an untreated partner, assuming that other reasons for a repeat positive test result are distributed equally between intervention and control arms. This outcome has been used in RCTs of PN interventions seeking to demonstrate prevention of transmission at the level of the individual.^16^

Secondary clinical outcomes are: (1) the proportion of sex partners treated 2 weeks after the initial PN consultation; (2) numbers of partners treated per index patient; (3) time to partner treatment and (4) number of patients notified per index patient. These outcomes will be ascertained by index patient reports at the 2-week follow-up telephone call with the research health adviser (RHA). Additional secondary outcomes include exploring the acceptability of the APT intervention to index patients and sex partners through qualitative telephone interviews with patients and partners as part of the process evaluation. We will determine rates of STI and HIV testing in sex partners and proportions of positive test results for STIs and HIV among sex partners who return postal self-sampling kits contained in APT packs. We will determine costs associated with the intervention in economic evaluation studies based on costings of the trial. We will record any adverse events using local activity logs at each trial site and report them to the trial sponsor and ethics committee.

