### Health economics evaluation

The aim of the economic evaluation is to determine the relative cost effectiveness of APT compared with standard PN. If APT reduces the number of re-infected cases, there will be cost implications for the healthcare sector and for society as a whole because of effects on the incidence of complications. Cost effectiveness will be determined in two ways using two separate economic analyses which will explore the costs and consequences of the alternative interventions and report results in terms of incremental cost effectiveness ratios if applicable. The two analyses are: (1) within trial economic evaluation which will report the terms of natural units including *cost per case of re-infection avoided* and (2) model-based economic evaluation which will report results in terms of cost per QALY (Quality-Adjusted Life Year) based on new data from recent research.^38^

The within trial evaluation will use only data collected within the trial and will draw on data collected through provision of APT up until 4 months postintervention when the index cases are re-tested. The evaluation will adopt the perspective of the NHS and will be based on an outcome of cost per case of re-infection avoided. It is acknowledged that this is an intermediate outcome. We will build on the experience of exploring the cost effectiveness of alternative versions of APT in previous exploratory and pilot studies.^25 26^

The trial will not capture the effects of APT on the transmission of chlamydia, or on female reproductive tract complications, such as PID. As for previous economic evaluations of chlamydia screening interventions,^39^ we will develop a dynamic model of the epidemiology of *C. trachomatis* transmission, the APT intervention and its outcomes, which will use data from the trial. The model-based economic evaluation and deterministic transmission dynamic model on which the economic evaluation will be based, will be reported in detail in a separate publication.

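### Three months after recruitment ends is too short to complete outcome collection for all phase-two patients, and the article does not say whether samples at 16–24 weeks count

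*Protocol article*

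**What the plan says.** The Outcomes section defines the primary outcome as a positive *C. trachomatis* test "12–16 weeks after the PN consultation". The Abstract, the objectives and the Sample size section use the same interval.

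Box 1, under Intervention, sets out how the sample is obtained. The kit is posted at 13 weeks and a text reminder follows 8 days after dispatch, "followed by a telephone call from the RHA 13 days after the self-sample kit is sent out". Patients may re-attend the clinic for testing instead. The one acceptance rule in Box 1 is "Self-samples received >24 weeks post-PN interview are excluded". It names self-samples and does not mention clinic re-tests. The Control section says that follow-up and repeat testing are the same in the control phase.

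The Trial timeline states that "patient recruitment is planned to end 17 November 2019" and gives a total duration of 19 months, "allowing for a 3-month follow-up period to enable outcome data collection to be completed for all patients in the second trial phase".

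**The concern.** There are two linked problems.

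First, the timeline claims that three months is enough to finish outcome collection for everyone in phase two. A kit that leaves at 13 weeks, with reminders to follow and a window running to at least 16 weeks, does not fit into three months. If the close-out were run as written, late phase-two recruits would have less time to return a sample than phase-one recruits. That adds missing data to a trial that already expects about 40% loss to follow-up, and it makes the timing of the outcome depend on period.

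Second, an analyst who follows the Outcomes section literally drops a sample received at 18 weeks. One who follows Box 1 keeps it. The choice can matter to the result, because the Introduction cites modelling that puts the peak incidence of repeat infection at 2–5 months after treatment. A test at 12 weeks and one at 24 weeks (about 5.5 months) therefore cover different parts of that period.

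**Working it through.** **Inputs.**
- Trial timeline: 4-month run-in (July–October 2018), trial start 22 October 2018, two 6-month phases, a 2-week washout, recruitment to 17 November 2019, 3 months of follow-up, 19 months in total.
- Box 1: kit at 13 weeks, text 8 days later, call 13 days after dispatch, self-samples accepted to 24 weeks.
- Outcomes: 12–16 weeks.
- Sample size: 17 clinics, 80 chlamydia-positive patients per clinic per phase, 60% giving a repeat sample.

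**The plan's own figure.** 4 + 6 + 6 + 3 = 19 months (19.5 with the washout). The three months is therefore a component of the stated duration when counted from the run-in. Counted from 22 October 2018, recruitment takes 391 days (12.8 months), and adding 3 gives 15.8 months, not 19. Nineteen months from that date ends on 22 May 2020, 26.7 weeks after the last recruit, which does not match a three-month follow-up.

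**Calendar for a patient recruited on 17 November 2019.**

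| Event | Days after recruitment | Date (2020) | Days relative to 17 Feb |
|---|---|---|---|
| Kit dispatched (13 weeks) | 91 | 16 Feb | −1 |
| Three months | 92 | 17 Feb | 0 |
| Text reminder | 99 | 24 Feb | +7 |
| Telephone call | 104 | 29 Feb | +12 |
| Week 16 | 112 | 8 Mar | +20 |
| Week 24 | 168 | 3 May | +76 |

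Three months ends one day after this patient's kit is posted.

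**Share of phase two with a shortened window, if three months is a hard close.** Share = days short ÷ length of phase two, assuming even accrual. The length is taken as 182 days (26 weeks) or 195 days (6 May to 17 November 2019, where 6 May is 22 October 2018 plus 6 months plus 2 weeks). Chlamydia-positive patients per phase: 17 × 80 = 1,360.
- 16 weeks (recruited after 28 October 2019): 20/195 = 10.3% and 20/182 = 11.0%, which is 139 to 149 patients.
- 24 weeks (recruited after 2 September 2019): 76/195 = 39.0% and 76/182 = 41.8%, which is 530 to 568 patients.

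At the plan's 60% return rate, the expected number of returners among them is 0.6 × 139 to 0.6 × 149 = about 84 to 90 for 16 weeks, and 0.6 × 530 to 0.6 × 568 = about 318 to 341 for 24 weeks. Only those whose sample would arrive after the close are affected. The article gives no return times, so that number cannot be calculated.

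**The two acceptance rules side by side, for self-samples.**

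| Sample received | Outcomes, read literally | Box 1 |
|---|---|---|
| 12–16 weeks | counts | counts |
| 16–24 weeks | does not count | counts |
| After 24 weeks | does not count | excluded |

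The call comes at 13 + 13/7 = 14.9 weeks. That leaves 112 − 104 = 8 days before week 16 for a chased patient to take, post and have a sample received, so the middle row may well contain samples.

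**Duration needed.** 112 days is 3.7 months and 168 days is 5.5 months. Counted from July 2018 with the washout, 4 + 6 + 0.5 + 6 + 3.7 = 20.2 months for 16 weeks, and about 22 months for 24 weeks.

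**The case against.** The strongest reply is that the plan has one outcome time, 12–16 weeks, stated consistently, with 24 weeks as an outer limit for late self-samples. Target times and acceptance limits often differ, and the link between them can be left to an analysis plan that is not shown. This largely stands. The rule is ambiguous for 16–24 weeks rather than absent. But the article states both limits and does not say which governs the primary dataset.

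A reader might infer that late phase-two patients are cut off on 17 February 2020. The documents do not support that. The timeline is a project schedule. No section says that later samples are rejected, that chasing stops or that the data are locked then. Box 1 points the other way, and the programme runs to March 2021. What stands is that the stated three months does not do what the timeline says it does.

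A reader might also take the phrases "chlamydia positive at 3 months" (Statistical analysis) and "up until 4 months postintervention when the index cases are re-tested" (Health economics evaluation) as further competing windows. They are better read as rounded labels: 12–16 weeks is about 2.8 to 3.7 months.

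Nor do the documents support a claim of bias between arms. Follow-up is the same in both conditions. Nine clinics deliver the intervention first and eight second, so phase two holds nine control and eight intervention clinics, and any shortening would fall almost equally on both arms.

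**Conclusion.** The point holds in two parts. The three-month follow-up cannot complete outcome collection for all phase-two patients under either limit. This follows from the stated dates and needs no assumption. Separately, the 12–16 week definition and the 24-week exclusion rule disagree on whether a self-sample at 16–24 weeks counts, and the 24-week rule does not mention clinic re-tests.

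The size is conditional. If three months were applied literally, about 10–11% of phase-two patients would lack a full 16-week window and about 39–42% a full 24-week window. This rests on even accrual and a phase two of 182 to 195 days. The figures count shortened windows and are not an estimate of lost outcomes. The main cost would be extra missing data and outcome timing that differs by period, not clear bias between arms.

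**What to change.** State one accepted sample window for the primary outcome, and apply it alike to self-samples and clinic re-tests and to both phases. One form that keeps the present wording is 12–16 weeks as the target time and 24 weeks as the outer limit, with an analysis restricted to 12–16 weeks as a sensitivity analysis. If the investigators intend 12–16 weeks as a strict limit, Box 1 should say so instead.

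Replace the three-month follow-up with a close-out date at which the last recruit reaches the chosen limit: 8 March 2020 for 16 weeks or 3 May 2020 for 24 weeks. Restate the 19 months to match, and say from which date it is counted.

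The cost is wording plus a later data lock: 20 days (about 3 weeks) for 16 weeks or 76 days (about 11 weeks) for 24 weeks. Both fit within a programme that runs to March 2021. The change needs no extra patients and no tests beyond those already planned.

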### Process evaluation

We will conduct an integrated process evaluation, which involves a suite of substudies with index patients, sex partners and healthcare professionals. In brief these studies include: (1) qualitative telephone interviews with a sample of index patients who accepted APT for one or more sex partner, which will take place up to 8 weeks after their first PN consultation; (2) qualitative telephone interviews with a sample of sex partners who received APT, up to 8 weeks after their APT consultation; (3) qualitative telephone interviews with healthcare professionals who delivered APT, which take place up to 16 weeks after the clinic offers APT during the intervention phase; (4) focus groups with healthcare professionals to explore the context, extent and fidelity of the intervention delivery, which will take place up to 16 weeks after the clinic offers APT during the intervention phase.

All potential participants will receive the relevant participant information sheet and the researcher will discuss this information with participants before seeking informed consent to participate (see online supplementary files 2–5). All telephone interviews will be audio-recorded with informed verbal consent prior to participation, transcribed verbatim and analysed using interpretative phenomenological analysis^36^ to understand lived experiences of using APT. The expected duration of telephone interviews is 30–60 min. Focus groups will be audio-recorded with informed written consent prior to participation, transcribed verbatim and data will be analysed using the Framework approach.^37^ Data collected will assess intervention fidelity, healthcare professionals’ APT training (the behaviour change techniques they received) and their experience of APT delivery (the behaviour change techniques they themselves delivered) in relation to a range of feasibility issues such as impact on clinic flow and wider systemic and cultural issues.

10.1136/bmjopen-2019-034806.supp2Supplementary data

10.1136/bmjopen-2019-034806.supp3Supplementary data

10.1136/bmjopen-2019-034806.supp4Supplementary data

10.1136/bmjopen-2019-034806.supp5Supplementary data

### Health economics evaluation

The aim of the economic evaluation is to determine the relative cost effectiveness of APT compared with standard PN. If APT reduces the number of re-infected cases, there will be cost implications for the healthcare sector and for society as a whole because of effects on the incidence of complications. Cost effectiveness will be determined in two ways using two separate economic analyses which will explore the costs and consequences of the alternative interventions and report results in terms of incremental cost effectiveness ratios if applicable. The two analyses are: (1) within trial economic evaluation which will report the terms of natural units including *cost per case of re-infection avoided* and (2) model-based economic evaluation which will report results in terms of cost per QALY (Quality-Adjusted Life Year) based on new data from recent research.^38^

The within trial evaluation will use only data collected within the trial and will draw on data collected through provision of APT up until 4 months postintervention when the index cases are re-tested. The evaluation will adopt the perspective of the NHS and will be based on an outcome of cost per case of re-infection avoided. It is acknowledged that this is an intermediate outcome. We will build on the experience of exploring the cost effectiveness of alternative versions of APT in previous exploratory and pilot studies.^25 26^

The trial will not capture the effects of APT on the transmission of chlamydia, or on female reproductive tract complications, such as PID. As for previous economic evaluations of chlamydia screening interventions,^39^ we will develop a dynamic model of the epidemiology of *C. trachomatis* transmission, the APT intervention and its outcomes, which will use data from the trial. The model-based economic evaluation and deterministic transmission dynamic model on which the economic evaluation will be based, will be reported in detail in a separate publication.

